## Abstract

Introduction: This is a presentation of a study protocol in order to evaluate whether the application of CO2 laser can additionally benefit the improvement of the symptoms of overactive bladder in postmenopausal women who have just started mirabegron as a treatment.

Materials and methods: This is a study protocol of a randomized double-blind placebo-controlled trial. A total of 50 menopausal women will participate in the study. All patients will start treatment with mirabegron 50 mg and will be randomized into two groups. Women in group A (control) will undergo CO2 laser treatments while those in group B (placebo group) will receive placebo CO2 laser treatments. In total, three monthly sessions will be held in both groups. The monitoring and evaluation of the results will be carried out by completing a three-day urination diary, as well as by completing the Female Lower Urinary Tract Symptoms, Overactive Bladder Questionnaire, King’s Health Questionnaire, Urinary Distress Inventory, Pelvic Floor Impact Questionnaire, Patient Global Impression of Improvement, before each session and a month after the last one. Differences between groups will be assessed at baseline and every month following the three laser therapies.

Results: This is an ongoing study protocol, and we are expecting the analysis of the results in 2024.

Conclusions: The use of laser CO2 in postmenopausal women with overactive bladder syndrome may be a well-tolerated alternative treatment. The goal of our study is to evaluate the efficacy of laser treatment in combination with b3-adrenoreceptor agonist therapy.

## Introduction

According to the International Continence Society (ICS), overactive bladder syndrome (OAB) is defined as urinary urgency with or without urinary incontinence, usually accompanied by frequency and nocturia [1]. OAB is a syndrome that can affect women of various ages and can have a negative impact in their social and sexual life.

The prevalence of OAB in women reaches 30-40% in Europe and USA and increases with age [2]. The age-dependent impact on OAB can be correlated with hypoestrogenism [3] as estrogens are acting on the receptors of the vagina, vulva, urethra and the bladder trigone, in order to maintain the collagen of the epithelium, moisturize the epithelial surfaces and maintain an adequate blood flow.

Initially OAB treatment includes conservative measures of pelvic floor muscle exercises, lifestyle, and behavioral modifications [4]. When these treatments are ineffective, initiation of pharmacological treatment is suggested. There are two classes of drug treatment, the antimuscarinics and the b3-adrenoreceptor agonists. The initial choice of medication therapy is based mostly on the side effects [5]. The antimuscarinics act on the muscarinic receptors and have possible adverse effects on the central nervous system (mouth dryness, constipation). B3-adrenoreceptor agonists act on the selective beta receptors of the detrusor muscle in order to enhance smooth muscle relaxation, presenting similar efficacy with the antimuscarinics with better tolerability.

Recently the use of fractioned CO2 laser seems to present an alternative option of a rapid, safe, and well tolerated treatment for OAB [6-8]. Although there is just a little evidence that can confirm the use of laser in patients with OAB, we presume that it may improve OAB symptoms by decreasing the urogenital age issues, since it seems that the regeneration effect involves all the layers of the vaginal wall, compared with estrogens that are acting superficially [9].

The aim of this study is to add more data to the scientific society by assessing the clinical efficacy and symptom relief of a combination therapy with b3-adrenoreceptor agonist (mirabegron 50mg) and vaginal fractional CO2 laser in post-menopausal women with OAB.

## Materials and methods

The study will be performed in an outpatient urogynecological unit of a tertiary referral center. Institutional Ethical Board was obtained for the present study (N.303) from 1st Department of Obstetrics & Gynecology, National and Kapodistrian University of Athens, Alexandra Hospital, Athens, and its protocol has been registered on ClinicalTrials.gov (NCT03846895). The Declaration of Helsinki was taken into consideration and all procedures comply with the EU General Data Protection Regulation. Potential modifications will be reviewed by the Institutional Ethics Committee and approvals will be obtained. Recruitment of participants will be performed in the urogynecology and the general gynecology outpatient departments. Screening, patient recruitment, and discussion of the study’s objectives and rationale, and obtainment of the signed informed consent forms will be performed by an independent to the study’s design physician. The study’s protocol is in accordance with the Standard Protocol Items: Recommendations for Interventional Trials (SPIRIT). The results of the study will be reported considering the Consolidated Standards of Reporting Trials (CONSORT) statement.

Study design

Initial assessment will include women in menopause who have been experiencing symptoms of overactive bladder. In order to evaluate the participation, patients have to fill in the International Consultation on Incontinence Questionnaire for the evaluation of the Female Lower Urinary Tract (ICIQ-FLUTS).

Symptoms (ICIQ-FLUTS) [10-11], a baseline demographic data, medical history and a three-day micturition diary, presenting the number of voids/incontinence, the volume of every micturition and the frequency of urge urination per day/24h. OAB will be defined by the void frequency and the episodes of urgent urination.

If the woman is eligible to participate, she will be asked to complete a three-day micturition diary for the previous week and fill in the Overactive Bladder Questionnaire (OABq), King’s Health Questionnaire (KHQ), Urinary Distress Inventory (UDI-6), and Pelvic Floor Impact Questionnaire (PFIQ) before every session. The Patient Global Impression of Improvement (PGI-I) questionnaire will be filled in only one time at the end of the study. All information will be evaluated in order to assess the improvement of frequency in micturition, urgent episodes and urinary incontinence, the impact of OAB symptoms on their quality of life, such as daily activities, relationships, feelings, botherness, personal and physical limitations and finally will be evaluated the patient’s impression of improvement one month after the last session in both groups.

The patients enrolled in the study must fulfill the following criteria shown in Table 1. Patients who cannot participate in the study are shown in Table 2.

**Table 1 TAB1:** Inclusion criteria FSH: follicle stimulating hormone

Inclusion Criteria
Postmenopausal women (≥12 months of amenorrhea or FSH ≥30-40 after total hysterectomy)
Overactive bladder syndrome: ≥three months symptoms of urgency, with or without urinary incontinence, and ≥eight episodes/24h
At least three episodes of urgent urination (3rd-4th grade) under PPiUS (patient perception intensity of urgency scale) during a three-day urination calendar, with or without urinary incontinence

**Table 2 TAB2:** Exclusion Criteria

Exclusion Criteria
Genital prolapse >2nd degree according to the Pelvic Organ Prolapse classification system
Voiding residue volume >200 ml
Obstruction bladder
Use of vaginal estrogen in the last month
Use of drugs for urinary incontinence
Use of psychiatric drugs
Urinary or genital infection
Kidney or liver disease
Cardiac conduction or rate disorders
Arterial hypertension unregulated
Neurological diseases and diabetic neuropathy
Myasthenia
Cancer
Previous radio-chemotherapy

Randomization

Eligible patients are randomized 1:1 using a computer-generated randomization scheme, to receive active laser therapy or placebo, once monthly for three months.

Interventions

All participants will receive treatment with mirabegron 50mg and they will equally be divided in active or placebo laser therapy. Fractional CO2 laser (SmartXide2 V2LR, Monalisa Touch, DEKA, Florence, Italy) will be applied at monthly intervals in both groups. The parameters of the machine can be changed manually and are presented in Table 3.

**Table 3 TAB3:** The machine laser parameters that are going to be used in each session of each group.

Laser Group	Placebo Group
Microablative fractional CO2 laser therapy at monthly intervals	Placebo CO2 laser therapies at monthly intervals
Power: 40 watts	Power: 0.5 watts
Dwell time: 1000μs	Dwell time: 1000μs
Spacing 1000 μm	Spacing 1000 μm
Depth: SmartStak parameter 3	Dwell time: 1000μs
D-pulse mode	Smart-pulse mode

Both groups will receive a total of three sessions. The technique of the vaginal therapy will be identical for both groups. The basic difference in parameters of these two groups are in power and emission mode.

Blinding

The investigator, study site personnel and patients will all be blinded to treatment. An unblinded nurse will be responsible for programming the laser parameters, before the doctor and patient enter the examination room. The screen of the laser system will be covered to ensure proper blinding. Although in the placebo group the power of 0.5 watts and smart pulse emission mode will not allow energy submission to the vaginal tissue, the identical laser sound and treatment technique as in the active group will cover the placebo procedure.

Data collection methods

The study consists of four clinical visits (months 0, 1, 2, 3). Demographics and other baseline characteristics will be collected at the start of run-in period (month 0). Patients will complete the questionnaires mentioned (OABq, KHQ, UDI-6, PFIQ) in every visit and a three-day micturition diary a week before it. In addition, the Patient Global Impression of Improvement questionnaire (PGI-I) will be added in the last visit. Patients are advised to record twice a day their blood pressure and pulse rate, a week before the randomization and at every visit.

Primary Outcomes

The primary outcomes will be assessed by the score of the OAB-q questionnaire that consists of an eihjt-item symptom bother scale section and a 25-item health-related quality of life scale section and by the completion of a three-day voiding diary, monitoring the frequency of micturition, the urgency, and the urinary incontinence.

Secondary Outcomes

The secondary outcomes will be assessed by the scores of the following validated questionnaires: 1) King’s Health Questionnaire (KHQ); 2) Urinary Distress Inventory (UDI-6); 3) Pelvic Floor Impact Questionnaire (PFIQ-7); 4) Patient Global Impression of Improvement (PGI-I).

Sample Size

Power analysis methodology represents a design, with two levels of the between-subject factor of two study groups and four levels of the within-subjects factor of time. A repeated measures ANOVA power analysis was conducted. The effect size for this calculation used the ratio of the standard deviation of the effects for a particular factor or interaction and the standard deviation of within-subject effects. The power analysis was conducted for a single, two-group between-subjects factor, and a single within-subjects factor assessed over four time points. For this design, 50 participants (25 per group) achieve a power of 0.80 for the within-subjects main effect at an effect size of 0.25; a power of 0.80 for the between-subjects main effect at an effect size of 0.32 and a power of 0.80 for the interaction effect at an effect size of 0.25.

Statistical analysis

Comparison of data between the compared groups in both phases will be based on the intention-to-treat principle. Randomisation will be done for all women. Later dropouts and those not adhering to protocol will be excluded. The normality assumption will be evaluated using the Kolmogorov-Smirnov test. Student’s t-tests will be computed for the comparison of a continuous variable between two groups when the distribution is normal and the Mann-Whitney test when the distribution is not normal. Paired t-tests and Wilcoxon signed rank tests will be used for pre and post comparisons. 

For the comparison of proportions between the two study groups, Chi-square and Fisher’s exact tests will be used. Repeated measurements ANOVA will be performed to evaluate the changes observed between control and intervention group over the follow-up period. Additionally, three sensitivity analyses will be performed: per-protocol analysis, robustness of trial accounting for missing data, and adjusting for baseline covariates. Per-protocol analysis will include women who will complete the therapeutic protocol.

Adjustment for confounding factors will be performed using mixed linear regression models that account for multiple measurements per individual obtained at different time points. All reported p values will be two-tailed and statistical significance is set at p<0.05.

Adverse effects

Patients with severe or uncontrolled hypertension should not take mirabegron and will be excluded from the study. While clinical trials have not demonstrated significant increases in blood pressure compared with placebo [12], patients can develop hypertension. Blood pressure will be monitored, and in case of any adverse event, blood pressure medications could be adjusted according to the primary care clinician's suggestion.

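### Four or five primary variables, monthly group comparisons and a flat two-sided 0.05, with no deciding variable, visit, test or success rule

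*Protocol article*

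**What the plan says.** Under Primary Outcomes (plural), the article states that "The primary outcomes will be assessed by the score of the OAB-q questionnaire". It describes that questionnaire as a symptom bother section plus "a 25-item health-related quality of life scale section". It adds that they will also be assessed "by the completion of a three-day voiding diary, monitoring the frequency of micturition, the urgency, and the urinary incontinence".

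Data collection methods sets visits at months 0, 1, 2 and 3, so three are post-baseline. The abstract says: "Differences between groups will be assessed at baseline and every month following the three laser therapies".

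Statistical analysis lists several ways to compare the groups. For two-group comparisons, "Student’s t-tests will be computed for the comparison of a continuous variable between two groups when the distribution is normal", with Mann-Whitney otherwise. It also plans a repeated-measures ANOVA over follow-up, and mixed linear models for adjustment. None of these is called the primary test. The only significance rule is "All reported p values will be two-tailed and statistical significance is set at p<0.05".

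Sample Size names no outcome variable. It claims power 0.80 for three separate effects: time, group, and their interaction.

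**The concern.** The article does not say what result would make the trial positive. Several variables have primary status, they are measured repeatedly, more than one type of test is planned, and every p value is judged at 0.05. Nothing puts the variables in order, requires all of them to succeed, or corrects for their number.

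A report that met every sentence of this text could claim success on whichever primary variable reached p<0.05. The 5% error rate would then hold for each test but not for the claim that laser adds to mirabegron. The Discussion says that earlier laser studies did not provide strong evidence. This trial has 25 women per group, and one nominally significant result among several uncorrected ones would not fill that gap.

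**Working it through.** **Inputs from the article.** Alpha 0.05 two-sided; 25 per group; four visits, three post-baseline; power 0.80 for the group effect at effect size f = 0.32. Primary variables: k = 5 (two OAB-q scales plus three diary variables), or k = 4 if OAB-q is a single score.

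**Assumed.** The correlation between variables and the correlation between visits are not given, so each is varied from 0 to 0.7. Within-subject correlation for the power check is set at 0.5.

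**1. The article's own power figure.** For the between-group effect in a repeated-measures ANOVA with m = 4 time points, the noncentrality is f² × N × m / (1 + (m − 1)ρ).
- 0.32² × 50 × 4 / (1 + 3 × 0.5) = 20.48 / 2.5 = 8.19.
- With 1 and 48 degrees of freedom and alpha 0.05, power is 0.801.

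The stated 0.80 reproduces. The calculation is for one test at 0.05 and allows nothing for several primaries.

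**2. Independent tests.** Chance of at least one false positive = 1 − 0.95^(number of tests).
- One visit, or one test per variable: 1 − 0.95⁴ = 18.5%; 1 − 0.95⁵ = 22.6%.
- Three visits: 1 − 0.95¹² = 46.0%; 1 − 0.95¹⁵ = 53.7%.

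**3. Correlated tests.** Multivariate-normal simulation with 400,000 draws, equal correlation between variables and equal correlation between visits, the two multiplied for pairs that differ in both:

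| Correlation between variables / visits | k = 4, one visit | k = 5, one visit | k = 4, any of three visits | k = 5, any of three visits |
|---|---|---|---|---|
| 0 / 0 | 18.5% | 23% | 46% | 54% |
| 0.3 / 0.5 | 17% | 21% | 39% | 46% |
| 0.5 / 0.5 | 16% | 18% | 36% | 41% |
| 0.5 / 0.7 | 16% | 18% | 31% | 36% |
| 0.7 / 0.5 | 13% | 15% | 30% | 34% |
| 0.7 / 0.7 | 13% | 15% | 27% | 30% |

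Simulated t-tests with 25 per arm (k = 5) agree. At 0.5/0.5 they give 18.6% at one visit and 41.4% over three; at 0.7/0.7 they give 15.2% and 30.4%.

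One repeated-measures test per variable gives four or five tests in all, so the one-visit columns apply to that reading too.

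**4. What a correction would cost.** For five primaries, Bonferroni alpha is 0.05 / 5 = 0.01.
- Repeated-measures group effect at f = 0.32 and ρ = 0.5: power at N = 50 falls from 0.80 to 0.57, and about N = 76 would be needed for 0.80.
- Plain comparison of 25 v 25 at one visit: the difference detectable with 80% power rises from 0.81 SD to 1.00 SD.

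**5. What naming one visit does to power.** With two equal groups, f = 0.32 corresponds to 2 × 0.32 = 0.64 SD. An unadjusted 25 v 25 comparison of that size at month 3 has about 60% power at alpha 0.05, not 80%.

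**The case against.** The strongest reply is that the article assigns the longitudinal comparison to a repeated-measures ANOVA and bases its sample size on the same model. On that reading there is one test per variable. The abstract says only that differences will be assessed monthly, and the t-test sentence names no visit. This stands as far as the count goes. A reader might infer that the plan commits to 15 primary tests with an error rate above 40%, but the text does not support that. Fifteen requires both the five-variable reading and a decisive test at every visit. Even then the rate falls to about 30% at correlations of 0.7, so 40% is not a floor. The reply does not remove the problem, because one test per variable still gives 13-23%.

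A second reply is that the article states no rule that any one variable suffices. That is true, and the percentages describe that rule, not one the plan has adopted. But the article does not state that all must succeed either, and nothing in it rules out the permissive reading.

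A third reply is that this is a condensed article, and a statistical analysis plan that is not shown may handle multiplicity. Leaving out the details of a correction would not be a finding. The finding is what the article does fix: several primaries and an unadjusted 0.05 for all reported p values. A later correction would have to override that sentence.

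**Conclusion.** The concern holds in this form: the article fixes several primary variables and one unadjusted threshold, and leaves open what decides the trial. If any single variable may do so, the family-wise error is about 13-23% at one visit or with one repeated-measures test per variable. It is roughly 27-54% if any of the three post-baseline visits also counts. Both ranges span four or five variables and correlations from 0 to 0.7, which are assumptions. Every scenario in the table is more than twice the nominal 5%. Under an all-must-succeed rule these figures would not apply, but the article states no such rule.

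This should be settled before unblinding, because a primary outcome chosen after the results are known would not be credible.

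**What to change.** Name one primary variable and one decisive test. For example: OAB-q symptom bother, with the between-group difference at month 3 (one month after the last session) estimated from the planned repeated-measures or mixed model, tested at two-sided 0.05. Make OAB-q quality of life, frequency, urgency and incontinence secondary, and treat months 1 and 2 as supportive. If the sponsor keeps all the variables as primary, define one comparison per variable and apply Holm across them.

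The change is to wording in the protocol, analysis plan and registration, and needs no new patients or data. It has two costs. The other variables lose primary status. The power statement must also be redone for the chosen test, because N = 50 was calculated for repeated-measures effects and a plain month-3 comparison would be weaker, as shown above. A model-based estimate may recover some of that loss, but by how much depends on correlations that the sponsor would have to state.

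### The stated power of 0.80 needs all 50 women in the analysis, but the plan excludes dropouts and non-adherers from those 50, against its own intention-to-treat statement

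*Protocol article*

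**What the plan says.** The Abstract of the protocol article sets enrolment: "A total of 50 menopausal women will participate in the study". The Sample Size section describes a repeated measures ANOVA with "two levels of the between-subject factor of two study groups and four levels of the within-subjects factor of time". For this design it reports three results, all at 50 participants:

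- within-subjects effect, at an effect size of 0.25: "50 participants (25 per group) achieve a power of 0.80"
- between-group effect: "a power of 0.80 for the between-subjects main effect at an effect size of 0.32"
- interaction: "a power of 0.80 for the interaction effect at an effect size of 0.25"

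The Statistical analysis section, which follows directly, adopts the intention-to-treat principle, says that all women are randomised, and then adds "Later dropouts and those not adhering to protocol will be excluded". It names repeated measures ANOVA for the comparison of the groups over follow-up. It lists per-protocol and missing-data analyses separately, as sensitivity analyses. Linear mixed models appear at the end of the section, for adjustment for confounding. The article gives no expected loss rate.

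**The concern.** Planned enrolment equals the number on which the power rests, and the analysis rule can only lower the number analysed. So the stated 0.80 describes a trial with no dropout and no non-adherence. The rule is also wider than ordinary attrition, because it removes women who stay in the trial but do not follow the protocol. The plan asks for three laser or placebo sessions, and for diaries and questionnaires at four visits, so some loss is plausible. The article itself plans for incomplete data in its sensitivity analyses.

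Two things are at stake. A null result would be read against a power that the trial may not have had. And excluding women after randomisation, for reasons that may be related to treatment or outcome, gives up the protection against bias that the intention-to-treat statement promises.

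**Working it through.** **Inputs from the article.** Two groups allocated 1:1, four time points (m = 4), two-sided significance level 0.05, N = 50, effect size f = 0.32 (between) and 0.25 (within and interaction), stated power 0.80 for each.

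**Inputs not in the article, hence assumed.** The correlation ρ between repeated measurements, the sphericity parameter ε, and the loss rate.

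**Step 1. Reproduce the between-group figure.** Noncentrality λ = f²·N·m / (1 + (m − 1)ρ), with 1 and N − 2 degrees of freedom. With ρ = 0.5 the denominator is 1 + 3 × 0.5 = 2.5, so λ = 0.1024 × 50 × 4 / 2.5 = 8.19. On 1 and 48 df the power is 0.801, which agrees with the stated 0.80. Other correlations do not reproduce it (ρ = 0.4 gives 0.848, ρ = 0.6 gives 0.755). At N = 49 the power is 0.792, so 50 is the smallest number that reaches 0.80.

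**Step 2. Apply the exclusion rule to the between-group effect.** Same formula, with N the number analysed:

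| Excluded | Analysed N | λ | Power |
|---|---|---|---|
| 0 | 50 | 8.19 | 0.801 |
| 1 | 49 | 8.03 | 0.792 |
| 2 | 48 | 7.86 | 0.784 |
| 3 | 47 | 7.70 | 0.775 |
| 5 (10%) | 45 | 7.37 | 0.756 |
| 10 (20%) | 40 | 6.55 | 0.704 |

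The power is more than two points below 0.80 from the third exclusion on.

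**Step 3. Detectable between-group effect at 0.80 power.** Solve λ for f: f = √(2.5·λ / (4N)), with λ the value that gives 0.80 at the given df.

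- N = 50: λ = 8.18, f = 0.32
- N = 45: λ = 8.22, f = √(2.5 × 8.22 / 180) = 0.34
- N = 40: λ = 8.27, f = √(2.5 × 8.27 / 160) = 0.36

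**Step 4. Interaction effect.** λ = f²·N·m·ε / (1 − ρ), with 3ε and 3ε(N − 2) df, at the stated f = 0.25:

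| Assumptions | N = 50 | N = 45 | N = 40 |
|---|---|---|---|
| ρ = 0.5, ε = 1/3 (lower bound) | 0.807 | 0.763 | 0.711 |
| ρ = 0, ε = 1 (full sphericity) | 0.846 | 0.800 | 0.745 |
| ρ = 0.5, ε = 1 (full sphericity) | 0.992 | 0.984 | 0.970 |

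The first row comes close to the stated 0.80 and leaves almost no slack. The other two start above 0.80 and still reach it at 10% loss; the third does so at 20% as well.

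**The case against.** Four points can be made for the plan.

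*The power figure is correct as stated.* It is given for 50 participants, and it reproduces. This stands: there is no slip in the calculation. The fault lies between the figure and the analysis rule.

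*A condensed article may leave the attrition allowance to the full protocol.* This also stands, and a missing allowance would not be a finding by itself. But the article states both the power at full enrolment and the exclusion rule, in adjacent sections, and those two statements conflict.

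*Intention-to-treat may be what governs.* If so, the losses in the tables would not apply in full. The article leaves this open. The exclusion follows the intention-to-treat statement directly, and the per-protocol analysis is listed apart, which suggests that the exclusion applies to the main analysis. One of the two sentences has to go on either reading.

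*The loss may be small.* Follow-up is three months and no loss rate is given. With one or two exclusions the between-group power is 0.792 or 0.784, within two points of the stated value.

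A reader might infer that any exclusion makes the trial materially underpowered, or that the interaction test must also fall below 0.80. The figures support neither. The first is not so for one or two women. The second does not follow, because the article does not state the correlation or sphericity, and under full sphericity 10% loss still leaves 0.80 or more.

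**Conclusion.** The point holds, conditionally. The stated power requires all 50 women, and the written analysis rule removes some of them, in contradiction to the principle stated just before it. For the between-group effect of 0.32 the design has no reserve: power is about 0.76 at 10% loss and 0.70 at 20%. This rests on a correlation of 0.5, the value that reproduces the article's figure, on assumed loss rates, and on excluded women contributing nothing.

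For the interaction effect a shortfall is possible but not established. A reader might also infer that the trial must enrol more women. That does not follow: a plan may keep 50 and state honestly what 50 can show. The contradiction between intention-to-treat and exclusion is the root of the matter, and the power loss is its consequence.

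**What to change.** 1. Delete the exclusion sentence and state that all randomised women are analysed in the group to which they were allocated.
2. Make the linear mixed model, already named in the Statistical analysis section for adjustment, the main group-by-time analysis in place of repeated measures ANOVA. Deleting the sentence is not enough, since repeated measures ANOVA in its standard form uses complete cases only. In the mixed model, women with partial follow-up contribute the visits they have.
3. Keep the exclusion of non-completers for the per-protocol sensitivity analysis only.
4. Restate the power, or the effect detectable with 0.80 power, at the number expected to have data, and give the assumed loss rate, correlation and sphericity. If 45 or 40 women are expected to have data, the detectable between-group effect is about 0.34 or 0.36 instead of 0.32. These values treat the remaining women as contributing nothing, so they are cautious once partial follow-up is used.

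The cost is a slightly less favourable power statement and a small change to the analysis text. No extra enrolment is needed.

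### The between-group power of 0.80 averages in the pre-laser visit, so it needs a post-treatment difference of about 0.85 SD rather than 0.64 SD

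*Protocol article*

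**What the plan says.** The Sample Size section of the protocol article describes a repeated measures ANOVA power analysis with "a single, two-group between-subjects factor, and a single within-subjects factor assessed over four time points". It reports three results: "For this design, 50 participants (25 per group) achieve a power of 0.80 for the within-subjects main effect at an effect size of 0.25", and then "a power of 0.80 for the between-subjects main effect at an effect size of 0.32 and a power of 0.80 for the interaction effect", the interaction also at 0.25. The effect size is defined as "the ratio of the standard deviation of the effects for a particular factor or interaction and the standard deviation of within-subject effects".

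Data collection methods fixes the time points: "The study consists of four clinical visits (months 0, 1, 2, 3"). The Abstract places the questionnaires and diary "before each session and a month after the last one", which makes the first assessment a pre-laser one.

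For the longitudinal comparison, Statistical analysis says: "Repeated measurements ANOVA will be performed to evaluate the changes observed between control and intervention group over the follow-up period". Adjustment for baseline covariates is listed there as one of three sensitivity analyses. The significance level is given at the end of the section: "All reported p values will be two-tailed and statistical significance is set at p<0.05".

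**The concern.** The trial asks whether laser adds to mirabegron. Of the three powered effects, the between-subjects main effect looks like the direct answer. It compares the arms on the average of all four visits, and at one of those visits neither arm has had laser. Month 0 adds no treatment signal to that average but takes a quarter of the weight.

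The consequence is for interpretation. Someone who reads f = 0.32 as the detectable laser effect would take the trial to have 80% power for a post-treatment difference of 0.64 SD. The main-effect test does not have that.

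A second, smaller problem is that the three powers respond differently to the within-woman correlation and to departures from sphericity. Whether they belong together depends on values that the paragraph does not give.

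**Working it through.** **Inputs.** From the article: N = 50, 2 groups of 25, m = 4 visits, f = 0.32 (between), f = 0.25 (time and interaction), two-sided alpha 0.05. Assumed, because not given: a common correlation r between visits, equal variances, and a sphericity factor epsilon (1 = sphericity; 1/3 = lower bound for four visits). All powers are from the noncentral F distribution.

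**1. Reproducing the stated figures, f in per-visit SD units**

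- Between: lambda = f²·N·m / (1 + 3r), df 1 and 48.
- Time and interaction: lambda = f²·N·m·epsilon / (1 − r), df 3·epsilon and 144·epsilon.

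Between, f = 0.32: at r = 0.5, lambda = 0.1024 × 200 / 2.5 = 8.19, power 0.801. At r = 0.3 power is 0.90 and at r = 0.7 it is 0.71. So 0.80 points to r of about 0.5.

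Time and interaction, f = 0.25:

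| r | epsilon | power |
|---|---|---|
| 0 | 1 | 0.846 |
| 0.5 | 1 | 0.99 |
| 0.5 | 1/3 | 0.807 |

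Under sphericity the figures disagree. With r = 0.5 and epsilon = 1/3 all three are close to 0.80.

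**2. The same, with f scaled to the within-subject SD as the text defines it**

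- Between: lambda = 0.1024 × 200 × (1 − r)/(1 + 3r) = 20.48(1 − r)/(1 + 3r). At r = 0.27 this is 8.26, power 0.804. At r = 0.5 power is 0.51.
- Time and interaction: lambda = 0.0625 × 200 × epsilon = 12.5·epsilon, whatever r is. Power is 0.846 at epsilon = 1 and 0.802 at epsilon = 0.86.

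Again all three agree, but only at r of about 0.27 with epsilon of about 0.86.

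**3. Dilution by month 0**

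With two equal groups f = d/2, so f = 0.32 is d = 0.64 SD averaged over four visits. With no difference at month 0 and a constant difference D at months 1-3, the four-visit average is (0 + 3D)/4 = 0.75D.

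- To reach 0.64 on average: D = 0.64 / 0.75 = 0.85 SD.
- If D = 0.64: the average is 0.48 SD, so f = 0.24 and lambda = 0.0576 × 200 / (1 + 3r) = 11.52 / (1 + 3r).

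| r | lambda | group main effect, 4 visits | group main effect, months 1-3 only |
|---|---|---|---|
| 0.3 | 6.06 | 0.67 | 0.86 |
| 0.5 | 4.61 | 0.56 | 0.78 |
| 0.7 | 3.72 | 0.47 | 0.70 |

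The factor 3/4 does not depend on the scaling of f. On the text's scaling at r = 0.27, lambda = 0.0576 × 200 × 0.73/1.81 = 4.65 and power falls from 0.80 to 0.56.

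**4. The interaction test for the same effect**

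The pattern 0, 1, 1, 1 has SD 0.433, so f = 0.32 × 0.433 = 0.139. Under sphericity, lambda = 0.0192 × 200 / (1 − r) = 5.49, 7.68 or 12.80, and power is 0.47, 0.62 or 0.85 at r = 0.3, 0.5 or 0.7. With epsilon = 1/3, the value that reconciles the figures in step 1, it is 0.26, 0.35 or 0.53. For this pattern the powered f = 0.25 corresponds to 0.5 / 0.433 = 1.15 SD.

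**5. Baseline-adjusted contrasts, 50 analysed, df 1 and 47**

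- Mean of months 1-3: residual variance v = (1 + 2r)/3 − r² = 0.443, 0.417 or 0.310. Lambda = 0.64² × 12.5 / v = 11.5, 12.3 or 16.5; power 0.91, 0.93 or 0.98.
- Month 3 alone: residual variance 1 − r². Power of 80% needs lambda of about 8.18, so d = √(8.18(1 − r²)/12.5) = 0.77, 0.70 or 0.58 SD. An unadjusted month-3 t-test needs 0.81 SD.

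**The case against.** The strongest reply is that the group main effect need not be the deciding test. The article says that repeated measures ANOVA will evaluate changes between the arms, which is naturally the group-by-time interaction. That effect is powered separately, and month 0 is its proper reference. This stands as a reading of the planned analysis, but it does not rescue the 0.80 for a sustained effect of 0.64 SD: the interaction reaches 0.80 only when r is high and sphericity holds (step 4). The article also plans baseline adjustment and mixed models, which recover the lost power, but it lists baseline adjustment as a sensitivity analysis and does not base the power statement on it.

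A reader might infer from step 1 that the three powers are arithmetically impossible together. The documents do not support that. Two sets of plausible software inputs reproduce them, one with a lower-bound correction and one with the text's own scaling and a mild correction. Neither is documented, so which was used cannot be known.

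Nor is the absence of r and epsilon from a journal article a fault by itself, since the full protocol may hold them. Reporting power for the time effect is not an error either. It does not compare the arms, and all women start mirabegron, so it says nothing about laser. The 0.64 SD is derived here from f; the article does not state it.

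**Conclusion.** The point holds for the month-0 dilution. The between-subjects figure of 0.80 at f = 0.32 corresponds to about 0.85 SD at months 1-3 on per-visit scaling. For a true 0.64 SD at months 1-3, main-effect power is roughly 0.67 to 0.47 over r = 0.3 to 0.7. This rests on no treatment difference at month 0, which follows from randomisation and the visit schedule, and on a constant effect afterwards. An effect that builds up over the sessions would be diluted further relative to its month-3 size. The correlations are assumed. The factor 3/4 does not depend on them.

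On the agreement of the three figures, the conclusion is limited: they conflict under sphericity and agree only at specific correlation and epsilon values that the article does not give.

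A reader might also conclude that 50 women are too few. That does not follow. With month 0 as a covariate, the same 50 women give power above 0.90 for 0.64 SD on the post-treatment mean. What needs correcting is the contrast that was powered.

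**What to change.** Treat month 0 as a covariate and not as a level of the group main effect. Replace the three-part power statement with one for a single baseline-adjusted between-arm contrast, either month 3 or the mean of months 1-3. State the assumed r, the analysed N and, if one was used, the sphericity correction. The analysed N needs stating because the Statistical analysis section removes later dropouts and non-adherent women. The figures in step 5 can be used as they stand if 50 are analysed. Removing the time main effect from the paragraph is optional.

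The cost is one rewritten paragraph and moving baseline adjustment from a sensitivity analysis to the chosen contrast. It uses data already collected and leaves the sample size at 50. The drawback is that, if month 3 is chosen, the stated detectable difference looks less favourable when r is low: 0.77 SD at r = 0.3, against the 0.64 SD that f = 0.32 suggests.
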